**Figure 1. f1:**
[figure not shown]
Consolidated standards of reporting clinical trial (CONSORT) flow chart. *PIH: Pregnancy Induced Hypertension, *GDM: Gestational Diabetes Mellitus, *VAS: Visual Anologue scale, WHO: World Health Organization. *SNOSEs: Sequentially Numbered Opaque and Sealed Envelopes, *QACE: Questionnaire on Assessing the Childbirth Experiences.

### Study setting and population

This study will be conducted in labor theatre of selected tertiary care hospital from Udupi District, Karnataka, India. Udupi district is hailed as one of the most progressive districts in the state about women and their empowerment. The percentage of women receiving antenatal care in the district according to 2011 census is 79.76% and share of institutional deliveries are 99.76%. Total bed strength of the selected tertiary care Hospital is 2400. Obstetrical and Gynecological (OBG) department is a multi-specialty department providing high-quality patient care and consists of a well- qualified team of Obstetricians and Gynecologists divided into 5 units and are dedicated to providing excellence. OBG department itself has a total of 250 beds with trained staff nurses with 1:1 staff patient ratio in Labor wards, to take care of any adverse effects at the time of intervention. Labor ward has 20 beds with well-equipped which contains Fetal heart rate monitoring machine (NST Machine) and tocography to record the uterine contractions. Population for the study is all low risk primigravid antenatal women admitted in labor theatre for labor or elective labor induction. An estimated 768 low-risk primigravid women will be recruited. This research is approved by Manipal Academy of Higher Education, Institutional review board (Reg no. ECR/146/Inst/KA/2013/RR-16).

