## Background

Even after the strong recommendations of the
World Health Organization regarding mobility and upright positions to prevent delay in the first stage of labor, increase in induction during labor, and continuous fetal monitoring (
Calik *et al.*, 2018) made position changes challenging during labor. Even if a mother is constrained to bed, frequent changes of maternal positions that facilitate pelvic movements should be given during labor (
Lawrence *et al.*, 2013). The absence of changes in the position of the mother during labor can lead to prolonged labor and increases the chance of cesarean birth due to failure to progress or descend (
Zwelling, 2010;
Akyıldız *et al.*, 2021). The peanut ball is considered an effective intervention to overcome this obstacle and promote the different positions during labor.

The peanut ball is an alternative to the conventional birth ball. The birthing ball is preferably used during the pregnancy period (
Ghasab *et al.*, 2019;
Mirzakhani *et al.*, 2015), whereas the effectiveness of the peanut ball is elicited even during labor (
Outland & Alvarado, 2019). The peanut ball is a curved peanut-shaped ball that has a middle indentation that allows the women to place the ball between and below the knees for allowing either the lateral, supine or sitting position, which increases pelvic dimensions, promotes progressive fetal rotation and descent during second-stage labor and ultimately promote the progress of labor (
Zwelling, 2010;
Roth *et al.*, 2016). Several studies have shown a reduction in either the length of labor (
Roth *et al.*, 2016;
Tussey CM, 2015) or a reduction in the cesarean birth (
Outland & Alvarado, 2019) with use of the peanut ball in immobile women.

In 2015, Tussey
*et al.* reported in a randomised controlled trial that effective utilisation of peanut ball during labor in the epidural woman has shortened the second stage of labor by 11 minutes and reached clinical significance in decreasing the length of time of the second stage of labor by 29 minutes. In addition, only 10% of those women who delivered with a peanut ball had a caesareans birth compared to 21% in the control group (p < .05) (
Tussey CM, 2015).

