## Methods

### Study design

A prospective block randomised controlled trial with parallel groups is the research design adopted for the study. Block randomisation of 64 blocks with a block size of 12 each is generated using a Research randomiser, an
online random number generator by a study statistician. A senior nurse who is working in the labor ward and who is not directly involved in the study will be generating the sequence. Concealment allocation will be achieved using a sequentially numbered opaque and
sealed envelope (SNOSE), where participants will be assigned randomly either to receive the peanut ball intervention or standard care.

All study materials can be found as
*Extended data* (
[name], 2022a–
f). The study will adhere to the Consolidated Standards of Reporting Trials (CONSORT) guidelines (
Figure 1) (
Sally Hopewell, 2008) and the protocol follows the Standard Protocol Items: Recommendations for Interventional Trials (SPIRIT) guidelines (
[name], 2022g).

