### Participant allocation/randomisation

Subsequently, the low risk primigravid women at 2–3 cm of cervical dilatation preferring a vaginal delivery will be block randomised to peanut ball intervention group or standard care control group by an external member (labor room nurse) with the help of SNOSEs. The research assistant and research nurse carrying out data collection, data entry, and data analysis will be blinded to group allocation.

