### Data analysis

Statistical analysis will be performed using
SPSS software version 16. The data analysis will be done based on the objectives and hypotheses of the study. We will follow the intention to treat analysis (ITT). The sample characteristics are measured using descriptive statistics. Two independent samples t-test/Mann-Whitney U-test (based on normality of data) will be used to determine the effectiveness of the usage of peanut ball on the maternal outcomes of labor. Associations among the variables will be computed using the Chi-square test (for categorical variables) and two independent samples t-test/Mann-Whitney U-test or one-way ANOVA/Kruskal Wallis test (for continuous variables). A comparison of behavioural response and stress level of low-risk primigravid women among experimental and control groups will be done using repeated measures of ANOVA. A comparison of childbirth experiences will be done using an independent t-test.

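### Adjusting the duration comparisons for onset of labour, which is known before randomisation, could add precision at little cost; the unadjusted tests are valid

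*Protocol article*

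**What the plan says.** Under Study setting and population, the protocol article admits two kinds of labour: "Population for the study is all low risk primigravid antenatal women admitted in labor theatre for labor or elective labor induction". It does not say what share is expected to be induced.

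Allocation comes later. Under Participant allocation/randomisation, "the low risk primigravid women at 2–3 cm of cervical dilatation preferring a vaginal delivery will be block randomised". The Study design section describes the list: "Block randomisation of 64 blocks with a block size of 12 each is generated using a Research randomiser". No stratification factor is named.

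The Data analysis section assigns these tests:

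- Maternal outcomes of labour: "Two independent samples t-test/Mann-Whitney U-test (based on normality of data) will be used to determine the effectiveness".
- Categorical variables: "Associations among the variables will be computed using the Chi-square test (for categorical variables").
- Behavioural response and stress level: "A comparison of behavioural response and stress level of low-risk primigravid women among experimental and control groups will be done using repeated measures of ANOVA".

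No covariate is attached to any of them. The Background names "increase in induction during labor, and continuous fetal monitoring" among the things that make position changes difficult. It then says that a lack of position changes can prolong labour and raise the chance of caesarean birth.

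**The concern.** Reason for admission is fixed before the envelope is opened. It cannot be affected by allocation, so it is a legitimate covariate. On the protocol's own reasoning, induction restricts movement and restricted movement prolongs labour. It is therefore plausible, though not shown, that onset predicts duration.

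Randomisation balances onset on average, but balance does not remove the variation that onset causes within each arm. In a covariate-free comparison that variation is counted as noise. If onset does predict duration, the confidence intervals are wider and the power lower than the same women could provide. Active-stage and second-stage duration are the outcomes most exposed, because they have no baseline measurement that could absorb the difference.

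**Working it through.** **Inputs from the document (Sample-size section).** SD 2.58 μg/dl for maternal serum cortisol, difference 0.55 μg/dl, z-values 1.96 and 0.84, attrition 10%, two equal arms.

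**The plan's own figure.** n per arm = 2 × (1.96 + 0.84)² × 2.58² / 0.55² = 345.03, taken as 345. Then 345 / 0.9 = 383.3, rounded up to 384 per arm, and 2 × 384 = 768. The stated total is reproduced. With unrounded normal quantiles the formula gives 346 per arm.

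**Unadjusted power.** With 345 per arm the standard error is 2.58 × √(2/345) = 0.1964. Since 0.55 / 0.1964 = 2.80, power = Φ(2.80 − 1.96) = 80.0%.

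**Effect of adjusting.** Let p be the share induced and D the mean difference between onset types in SD units. Both are assumptions. Onset then explains R² = p(1 − p)D² of the variance, and the residual SD is 2.58 × √(1 − R²). For example, p = 0.5 and D = 1 give R² = 0.25, residual SD 2.234 and standard error 0.1701. Then 0.55 / 0.1701 = 3.23, and power = Φ(3.23 − 1.96), about 89.9%.

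In each range below, the first value is for p = 10% and the second for p = 50%:

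| D (SD) | R² | Power, 345 per arm | n per arm for 80% |
|---|---|---|---|
| 0 | 0 | 80.0% | 346 |
| 0.2 | 0.4–1.0% | 80.1–80.4% | 345–342 |
| 0.5 | 2.3–6.3% | 80.8–82.4% | 338–324 |
| 1.0 | 9–25% | 83.5–89.9% | 315–260 |

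**How far this carries over.** These powers depend only on the standardised difference, 0.55 / 2.58 = 0.213. They illustrate any outcome measured once with an effect of that size. The document gives no SD or target difference for the durations, so the table shows the order of the gain and is not a power statement for them.

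**Cost in the worst case.** If D = 0, one degree of freedom out of about 690 is lost, and the variance rises by about 1/686 = 0.15%.

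**Simulation check (345 per arm, 4,000 runs per setting).** Type I error was 4.7–5.1% unadjusted and 4.6–5.4% adjusted. Power, unadjusted against adjusted:

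- D = 0, p = 0.3: 80.7% and 80.7%
- D = 0.2, p = 0.3: 79.4% and 79.7%
- D = 0.5, p = 0.3: 80.2% and 81.8%
- D = 0.5, p = 0.5: 79.5% and 81.5%
- D = 1.0, p = 0.5: 78.9% and 89.4%

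**Caesarean.** A logistic model with onset changes the quantity estimated. Assume a 20% risk in spontaneous controls, an odds ratio of 3 for onset, and half induced. A conditional odds ratio of 0.50 for the intervention then corresponds to a marginal one of 0.518.

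**The case against.** The strongest objection is that nothing in the plan is wrong here. A covariate-free comparison of randomised arms is unbiased and keeps its error rate, and 768 follows from the plan's own inputs for exactly that comparison. This stands, and it limits the point to efficiency. A reader might infer that mixing spontaneous and induced labours biases the result or invalidates the sample size. The document supports neither inference.

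Second, the gain is not known to exist. The Background ties induction to restricted position changes in words only; no figure links onset to any outcome. A reader might assume that onset explains 5–20% of the variance and conclude that power rises to 82–88%. Reaching 20% needs an onset difference of about 0.9 SD with half induced, since √(0.20/0.25) = 0.89, and 1.5 SD with 10% induced, since √(0.20/0.09) = 1.49. Nothing in the document supports effects of that size, so the range must start at nil.

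Third, cortisol, the outcome used for sizing, is measured twice in labour, and stress level is assigned to repeated measures ANOVA. Read as a group-by-time analysis, this already cancels any onset effect that is the same at both samples. The table therefore does not describe the planned cortisol analysis.

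Fourth, the Background remark could be read as saying that the ball works differently in induced labour. That would be effect modification, which a main-effect covariate does not address, and it is not claimed here.

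Fifth, adjustment has costs: the rank-test provision is lost, and the odds ratio for caesarean becomes conditional. Both are real and are handled in the fix.

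Finally, covariates may be set in a full protocol or analysis plan that is not shown. That is possible, but the article does assign specific covariate-free tests, and the recommendation concerns those stated tests.

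**Conclusion.** The point holds as a minor efficiency recommendation. Onset type is mixed by design and known before allocation, and neither the randomisation nor any named test uses it. The present tests remain valid.

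The case is best for active-stage and second-stage duration. For a single-measurement comparison starting at 80% power, the gain runs from nil to about 10 percentage points. It is negligible up to an onset difference of 0.2 SD and about 1–2 points at 0.5 SD. It approaches 10 points only at 1 SD with half the women induced. For cortisol under a group-by-time analysis it would be smaller. All of these sizes rest on assumed values for the share induced and the onset effect.

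**What to change.** Before analysis, prespecify onset of labour (spontaneous or elective induction, as recorded at admission before randomisation) as a covariate:

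- **Durations.** Use linear models for active-stage and second-stage duration with terms for arm and onset. If the durations are skewed, use a log scale or robust standard errors in place of switching to Mann-Whitney.
- **Cortisol.** Add onset as a covariate in the cortisol model.
- **Caesarean, if adjusted.** Report a standardised risk difference, or state that the odds ratio is conditional on onset.

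The cost is one field from the admission record if it is not already collected, one degree of freedom, and replacement of the rank test by a model. The randomisation list, the sample size and patient care do not change. The Discussion describes recruitment as still short of the target, so the change can be fixed before the data are analysed.

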### Eligibility criteria

The eligibility criteria include low-risk primigravid women who are aged between 18 to 40 years, singleton pregnancy and in cephalic presentation, gestational age of 37.0 to 41.6 weeks, well-controlled pre-eclampsia, and gestational diabetes mellitus, history of abortions, well-controlled/moderate anaemia, history of mild intrauterine growth restriction (IUGR), willing to use the peanut ball during the first stage of labor and preferring a vaginal delivery.

### Exclusion criteria

The exclusion criteria include women who are known to have any major fetal anomalies and very low and late preterm, a high-risk antenatal mother with any pregnancy-related complications like severe pre-eclampsia/eclampsia, preterm labor, placenta praevia, malpresentation during the study, contraindication for vaginal delivery, multigravida, multiple pregnancies, had any sort of fracture of leg/any major problem in the past and having weight more than 90 kg.

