### Recruitment and consent

All the low-risk primigravid women at or after 37 weeks of gestation attending the outpatient services at tertiary care hospitals for an antenatal check-up will be oriented about the implementation of peanut ball during labor by using the peanut ball positions chart prepared by
premier birth tools and by showing the video on peanut ball during labor prepared by the researcher.

Thereafter, the mothers will be screened in the labor room based on the inclusion criteria. The research team will explain the research purpose and procedure to the eligible mothers and, if they are willing to participate, informed written consent will be taken.

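### The exclusion for malpresentation arising during the study allows women to be excluded after randomisation, which conflicts with the stated intention-to-treat analysis

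*Protocol article*

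**What the plan says.** Under Exclusion criteria, the protocol article rules out "a high-risk antenatal mother with any pregnancy-related complications like severe pre-eclampsia/eclampsia, preterm labor, placenta praevia, malpresentation during the study". Under Eligibility criteria, it already requires "singleton pregnancy and in cephalic presentation".

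The order of events is given in three sections. Recruitment and consent states that "the mothers will be screened in the labor room based on the inclusion criteria". Participant allocation/randomisation states that "the low risk primigravid women at 2–3 cm of cervical dilatation preferring a vaginal delivery will be block randomised". The Intervention section starts the ball at 4 cm or later.

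On the analysis set, Data analysis says "We will follow the intention to treat analysis (ITT" and nothing further. The section on discontinuing deals with voluntary withdrawal and keeps the data gathered up to that point.

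On mechanism, the Background says that the ball "promotes progressive fetal rotation and descent during second-stage labor".

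On complications, the inclusion list admits women with "well-controlled pre-eclampsia, and gestational diabetes mellitus, history of abortions, well-controlled/moderate anaemia, history of mild intrauterine growth restriction (IUGR".

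**The concern.** An eligibility criterion should be settled before the envelope is opened. This one is dated to a period that runs past randomisation and through labour. If it is applied as written, a woman can be allocated, labour with or without the ball, be found to have a malpresentation, and then be classed as ineligible.

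Such an exclusion is not neutral. Malpresentation found in labour bears on how the baby is delivered, and the Abstract lists mode of delivery among the primary outcomes. If the ball changes how often malpresentation occurs, the women removed differ between arms because of treatment, and the comparison of those left is no longer protected by randomisation. The Discussion also says that investigators know the allocation, and the article does not say who would apply the clause.

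A smaller point concerns the same list. Its phrase about complications is open-ended, while the inclusion list admits several controlled or mild complications of pregnancy.

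**Working it through.** **Step 1: the timeline.**

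| Step | Protocol article section | Time |
|---|---|---|
| Screening and consent | Recruitment and consent | Labour room, before allocation |
| Randomisation | Participant allocation/randomisation | 2–3 cm |
| Ball positioning starts | Intervention | 4 cm or later |
| Malpresentation exclusion | Exclusion criteria | At any time in the study |

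Recruitment and consent mentions only the inclusion criteria. In the text available (the flow chart is not shown), no section fixes the moment at which the exclusions are applied.

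**Step 2: what the clause adds.** A woman must have a cephalic presentation to enter. A clause about presentation at screening would add little to that. The timing words give it a separate role, which is to cover malpresentation found later.

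**Step 3: is there a rule that resolves it?** Data analysis says ITT, which would keep a randomised woman in her arm. Exclusion criteria would make the same woman ineligible. The discontinuation section could decide between them, but it addresses only women who choose to withdraw. The conflict stays open.

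**Step 4: possible size (illustration only).** The documents give no malpresentation rate, so I assumed a range.

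Inputs:
- Women per arm: 384. The sample-size formula gives 2 × (1.96 + 0.84)² × 2.58² / 0.55² = 345.03 per group; 345.03 / 0.9 = 383.4, rounded up to 384; 2 × 384 = 768, which reproduces the stated total.
- Control caesarean rate: 21%, from the earlier trial cited in the Background, which was in women with epidurals.
- Malpresentation rates in the control and ball arms, m_c and m_b: assumed.
- Every malpresentation is delivered by caesarean, and all other women have the same caesarean rate p in both arms: assumed.

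Formulas:
- p = (0.21 − m_c) / (1 − m_c)
- True difference with everyone kept: D = (m_c − m_b)(1 − p)
- Difference after removing malpresentation cases: p − p = 0, so all of D is lost.

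| m_c, m_b | p | Women removed (control, ball) | D in points |
|---|---|---|---|
| 5%, 5% | 0.16/0.95 = 0.168 | 19, 19 | 0 |
| 2%, 1% | 0.19/0.98 = 0.194 | 8, 4 | 0.010 × 0.806 → 0.8 |
| 5%, 2.5% | 0.16/0.95 = 0.168 | 19, 10 | 0.025 × 0.832 → 2.1 |
| 8%, 4% | 0.13/0.92 = 0.141 | 31, 15 | 0.040 × 0.859 → 3.4 |

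The cited earlier trial reported 21% versus 10%, a gap of 11 points. The last three rows are about 7%, 19% and 31% of that gap.

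**Step 5: power is not the issue.** For the cortisol difference used in the sample size, power is 80.0% if 10% of each arm is lost and 79.1% if 12% is lost. What matters is which women are removed, more than how many.

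**The case against.** The strongest case on the other side has four parts.

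- **The clause sits in an eligibility list.** That list opens with conditions known at recruitment, and screening comes before consent and allocation. The sponsor may have meant only women whose malpresentation is known by then. This may be so, but the timing words say otherwise and nothing corrects them.
- **No passage says that a randomised woman is dropped from the analysis.** This is correct. A reader might infer that the protocol plans such removal; it does not say so, and it states ITT. The fault is that the wording permits removal. The article is condensed and an analysis plan is not shown, but the point is not that detail is missing: two statements in the article pull in different directions.
- **The Background speaks of rotation and descent, not of presentation.** This also stands. A reader might infer that the protocol claims the ball prevents malpresentation; it does not. A link to treatment is plausible from the stated mechanism, and no more than that.
- **Keeping these women does not rescue every outcome.** The second maternal cortisol sample is taken at full dilatation, so a woman delivered by caesarean before then has no second value under either rule. The gain from keeping her is clearest for mode of delivery.

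A reader might also infer that the two lists contradict each other on complications, since pre-eclampsia and gestational diabetes are themselves complications of pregnancy. The text does not support that. The exclusion is tied to high-risk women and gives severe disease as its example; the inclusion list admits controlled disease or a history of mild disease. The two can be read together. What remains is loose wording that leaves some cases to the screener. Nor is there a clash with the hypotheses, none of which uses the low-risk label.

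**Conclusion.** The point holds for the malpresentation clause. As written, it permits exclusion after randomisation for an event in labour that is tied to mode of delivery and may be related to treatment. It conflicts with the stated ITT analysis, and no other section resolves the conflict. It should be corrected.

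The size of any bias is unknown. The range of 0 to 3.4 points rests on assumed malpresentation rates, on caesarean delivery in every such case, and on a control rate borrowed from a different population. It shows only that the effect could run from nothing to a noticeable share of the differences seen before. The defect in wording does not depend on it.

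The Discussion reports 550 women randomised but 225 in each arm, and 225 + 225 = 450. A reader might infer that women have already been removed under this clause. The article gives no reason for the gap, which may be a simple error, so that inference is not supported.

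The complications wording is a secondary ambiguity.

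**What to change.** 1. Delete the three timing words that follow malpresentation in the exclusion list, and state that presentation is assessed for eligibility only at or before randomisation.
2. State under Data analysis that women found to have a malpresentation after randomisation stay in their allocated arm in the ITT analysis. This concerns the analysis set only and leaves their care unchanged.
3. Report, by arm, the number of women already excluded for this reason, and recover their outcome data where possible.
4. Reconcile the open phrase on complications with the controlled or mild conditions that the inclusion list admits, so that each condition falls clearly on one side.

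The cost is small: a wording amendment and one analysis rule, with no change to treatment, assessments or sample size. A few women stay in the analysis who would otherwise be dropped. With recruitment well advanced, the amendment cannot change who was admitted, and the main effort would be tracing data for any woman already excluded.
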